### Data analysis

#### Phase 1

To perform the process of qualitative content analysis, the audio file of each interview will be listened to attentively several times on the same day and it will be transcribed verbatim. To keep the data from the interviews confidential, a code will be assigned to each transcript. To come up with a general impression of the interviews and become fully immersed in the data, the audio files of the interviews and the transcripts will be reviewed several times, and any possible ambiguities and inconsistencies will be removed by comparing the audio files and the transcripts. The interviews will be audiotaped and a summary of the key issues in each interview will be then sent to each participant to ensure that the researcher will have accurately interpreted that participant’s comments (a “member check”) [26]. The process of data analysis will be performed continuously and simultaneously with the data collection process. All words, sentences, and paragraphs that are related in the analysis process will be considered as a single semantic unit. After merging the semantic units, the codes will be extracted. The codes together form the subcategories and then the main categories. Finally, upon the abstraction of the categories, the relevant themes will be identified. MAX.QDA software will be used to manage the data [40].

#### Phase 2

The collected data will be analyzed with SPSS software using descriptive statistics (including frequency, frequency percentage, mean, and standard deviation) and inferential statistics. We will undertake both “intention to treat” and “per protocol” approaches to the inferential statistical analyses to achieve fully understand the outcomes and manage bias in the face of any drop out. To compare the differences between the values obtained before the intervention and 3 and 6 months after the intervention in each group, generalized mixed models of analysis of variance for repeated measures will be used. We will also calculate differences between means of the independent groups with their respective 95% confidence intervals. All tests will be performed at a significance level of 0.05 (p <0.05). The Kolmogorov-Smirnov test will be used to test the normality of the data. The per protocol analyses will only include the participants who complete the intervention to which they were allocated.

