Based on the literature, it is presumed that this training interventional program will improve the HRQOL and work ability of housewives, and also that the severity of WMSDs and stress will be improved in the intervention groups relative to the control group. We also hypothesize that the use of a mixed biomechanical and psychosocial risk reduction interventional program will have an additive effective and this program will be more effective than each of the two separate intervention programs to reduce WMSDs and stress and improve the HRQOL and work ability consequences.

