**Inclusion criteria**	
Working-aged woman aged 20–65 years	
Diagnosed MSD and an MSD pain intensity score of 4 and higher based on the visual analog scale (VAS) [25, 26].	
The motivation and willingness to fully participate with any randomly allocated intervention	
Being married and living with the family	
Having no job other than housekeeping	
Not pregnant, nor breastfeeding	

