### The intervention programs

The conceptual framework of the health promotion model will be developed based on phase 1 findings from the qualitative study. Recruitment of women who meet the inclusion criteria will continue until the required sample size is achieved. At this point, all participants will be coded and blindly allocated into one of four intervention groups by the researchers using a permuted block randomization program: (1) biomechanical, (2) psychosocial, (3) multidisciplinary (biomechanical and psychosocial), or (4) control. Based on the design of the randomized controlled trial intervention, the impact of the different intervention programs on musculoskeletal disorders, work ability, and quality of life of the housewives will be evaluated. As shown in Fig. 1, measures will be collected at baseline, after 3 months, and after 6 months of following their respective program.

To implement the content of the three intervention programs, a participatory ergonomic approach will be used. The effectiveness of this approach in ergonomic interventions depends on the ability and active cooperation of participants [29]. The required training content for participants in the psychosocial intervention will be provided following the conceptual framework developed in the qualitative study and the resulting theory. Similarly, for participants in the biomechanical intervention group, the required training will be provided following the conceptual framework derived from the qualitative study and job safety analysis (JSA) method. Finally, the multidisciplinary intervention group will receive the training provided to the psychosocial and biomechanical groups: that is, they will do both interventions. The multidisciplinary groups will receive both of the other two interventions in full.

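### The only named model is aimed at change within each arm, although the trial's questions are between arms and no baseline-adjusted or group-by-time contrast is stated

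*Protocol article*

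**What the plan says.** In the Phase 2 part of Data analysis, the aim attached to the model is "To compare the differences between the values obtained before the intervention and 3 and 6 months after the intervention in each group", and for this "generalized mixed models of analysis of variance for repeated measures will be used". The next sentence turns to the arms: "We will also calculate differences between means of the independent groups with their respective 95% confidence intervals". It does not say whether these are means at follow-up, means of change or model-based means, at which visit they are taken, or whether baseline enters the estimate.

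The questions lie elsewhere in the article. The Background expects that "the severity of WMSDs and stress will be improved in the intervention groups relative to the control group", and says of the combined programme that "this program will be more effective than each of the two separate intervention programs". The research question under Secondary outcomes asks which of the three interventions is the most effective. The sample size section sizes the trial for a difference between groups.

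Baseline data will be available, since "measures will be collected at baseline, after 3 months, and after 6 months of following their respective program". One entry criterion is "an MSD pain intensity score of 4 and higher based on the visual analog scale", and the VAS is also one of the five outcome instruments.

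**The concern.** A test of change inside one arm does not compare a programme with control. Everything that moves scores over six months (natural recovery, repeat measurement, regression to the mean after entry on a pain threshold) is contained in it. Randomisation removes these influences only from a contrast between arms. Where the one named model is directed at within-arm change, the results most likely to be prominent are those that do not answer the trial's questions.

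The contrast that does answer them is described without any use of the baseline value. That leaves precision unused in a trial that may end with fewer than 30 women per arm.

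**Working it through.** **1. Purpose of the model against purpose of the trial**

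| Place in the protocol article | Comparison |
|---|---|
| Background, first hypothesis | Each intervention against control |
| Background, second hypothesis | Combined programme against each single programme |
| Secondary outcomes, research question | Which of three interventions is most effective |
| Sample size and power calculations | Difference between two group means |
| Data analysis, Phase 2, named model | Before against after, in each group |
| Data analysis, Phase 2, following sentence | Difference between group means with 95% CI, adjustment and visit not stated |

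**2. The plan's own figure**

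Inputs from the sample size section: SDs 20.2 and 21.1, difference 15, Z values 1.96 and 0.84.

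n = (1.96 + 0.84)² × (20.2² + 21.1²) / 15² = 7.84 × 853.25 / 225 = 29.73, which rounds up to the stated 30. (The printed intermediate value is 29.9; the rounded n is the same.) The formula is for an unadjusted comparison of two independent means, so the trial was sized on a between-arm contrast.

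**3. What baseline adjustment would add**

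- Average SD = √[(20.2² + 21.1²)/2] = 20.65, so d = 15/20.65 = 0.726.
- Women left per arm after the stated 30% dropout: 40 × 0.7 = 28.
- Adjusting for baseline multiplies the residual variance by 1 − r², so d becomes 0.726/√(1 − r²). The correlation r between baseline and follow-up is not in the document and is assumed.
- Power is from the two-sided two-sample t-test at 0.05.

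| Assumed r | Residual variance factor | d | Power at 28 per arm |
|---|---|---|---|
| unadjusted | 1.00 | 0.726 | 0.761 |
| 0.4 | 0.84 | 0.792 | 0.829 |
| 0.5 | 0.75 | 0.839 | 0.869 |
| 0.6 | 0.64 | 0.908 | 0.916 |

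With no dropout (40 per arm) the unadjusted power is 0.89.

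**4. How far pain VAS could fall with no treatment**

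All inputs here are assumptions except the cut-off of 4. The calculation also takes the screening score to be the analysis baseline.

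- Expected fall = (1 − r) × (E[X | X ≥ 4] − μ). With μ = 4, SD 2 and retest r = 0.6: E[X | X ≥ 4] = 4 + 2 × 0.798 = 5.596, so the fall is 0.4 × 1.596 = 0.64 points.
- Variance of change = (1 − r)² × Var(X | X ≥ 4) + SD²(1 − r²) = 0.16 × 1.454 + 4 × 0.64 = 2.79, SD 1.67.
- For 30 untreated women the standard error is 1.67/√30 = 0.305 and the noncentrality is 0.638/0.305 = 2.09. A paired t-test would then be significant with a chance of about 52%.
- Over means of 3 to 5 and r of 0.5 to 0.8 the chance runs from 14% to 92%. With a mean of 6 and r = 0.6 it is about 11%.

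**5. If within-arm tests were set side by side**

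Assume no true difference between arms, 30 per arm, r = 0.5 and the same change in every arm. The SD of change is 20.65 × √[2(1 − 0.5)] = 20.65. Let p be the chance that one arm is significant (normal approximation).

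| Common change | p | One given active arm significant, control not: p(1 − p) | At least one of three active arms significant, control not: [1 − (1 − p)³](1 − p) |
|---|---|---|---|
| 5 | 0.264 | 0.19 | 0.44 |
| 7.5 | 0.512 | 0.25 | 0.43 |
| 10 | 0.755 | 0.19 | 0.24 |

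At a common change of 15 points the last figure falls to 0.02, because nearly every arm is then significant.

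**The case against.** The wording can be read more kindly, and much of that reading stands.

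- A repeated-measures mixed model in a four-arm trial can carry group and group-by-time terms. The text does not exclude them, does not say that one model is fitted per arm, and an article need not list model terms.
- A reader might infer that the plan ignores the baseline. It does not: baseline is one of the three time points in the named model. What is unstated is its use in the between-arm estimate.
- A reader might infer that the between-arm difference is a raw one. The text does not say so; it is silent on adjustment.
- A reader might infer that the trial will rest its conclusions on uncontrolled change, or on one arm being significant and another not. Nothing in the document says that. There is a randomised control group, between-group differences with confidence intervals are planned, and both intention-to-treat and per-protocol analyses are announced. The side-by-side calculation shows a risk of a misreading, not something the plan proposes.
- An unadjusted randomised difference is unbiased, and its interval already allows for chance imbalance. Regression to the mean is common to the arms in expectation and does not bias that difference.
- The VAS calculation concerns one instrument of five, its inputs are not documented, and if baseline was measured afresh after screening, much of the fall would already have happened. The schedule that might settle this is a figure not shown.

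What remains is not mere silence. The article does state what the model is for, and the purpose it states differs from that of the hypotheses, the research question and the sample size.

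**Conclusion.** The point holds as a correctable mismatch, and a modest one. The single named model is pointed at within-arm change, while every question the trial poses is between arms, and the between-arm estimate is given no baseline adjustment, group-by-time contrast or visit. The planned between-group difference is valid.

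The quantified cost is precision: at 28 per arm and 15 points, power of 0.76 against 0.83 to 0.92. This rests on the protocol's SDs and dropout rate and on an assumed correlation of 0.4 to 0.6. With less dropout the shortfall is smaller.

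Regression to the mean in VAS is a sound reason not to test within-arm change, but its size cannot be fixed from this document; the 14% to 92% range shows how far it depends on the assumptions. It should not be used to grade the seriousness of the point.

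**What to change.** State as the main analysis one mixed model for the 3- and 6-month values, with arm, visit, arm-by-visit and the baseline value of the outcome as covariate. Report the baseline-adjusted differences between arms with 95% confidence intervals at a visit named in advance, covering each intervention against control and the combined programme against each single one. Present within-arm changes as description, without significance tests. State also whether the screening VAS serves as the baseline value.

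The cost is analysis wording only, since the baseline, 3-month and 6-month measurements are already planned. The change should be made before outcomes are analysed by arm.

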### Secondary outcomes

The effect of our educational intervention on the quality of life, ability to work, stress, and musculoskeletal problems.

Accordingly, the main research questions addressed in this study are as follows:
Which health education and health promotion model will be preferred for use among the housewives?We are testing three interventions: which intervention is the most effective for improving quality of life and work ability, and reducing WMSD symptoms and stress?

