### Sample size and power calculations

Following the study conducted by Shariat [37], which similarly used a three-arm, parallel, RCT to investigate MSDs in office workers, the sample size we require in the quantitative phase to provide ample power was calculated as 30 persons for each group. This sample size was calculated to be sufficient at an alpha of 0.05 and a power of .80, to test for a difference between the groups. Nevertheless, sample size calculations are sensitive to error and complicated when drawing upon incomplete information in the literature [38]. Additionally, experience indicated we must consider a potential dropout rate of 30%. Hence, according to the following formula, we should work with an initial recruitment target of 40 participants in each group:
$$ n=\frac{{\left({Z}_{1-\frac{\alpha }{2}}+{Z}_{1-\beta}\right)}^2\left({\delta_1}^2+{\delta_2}^2\right)}{{\left(\overline{{\overline{X}}_1}-{\overline{X}}_2\right)}^2}=\frac{{\left(1.96+0.84\right)}^2\left({20.2}^2+{21.1}^2\right)}{{\left(-15\right)}^2}=29.9\cong 30 $$

N=30+30(0.3)≅40

In line with this approach, a total of 160 housewives aged 20–65 years with WMSDs will be recruited based on the health records available in the health centers of Akbarabad-Kavar city by taking into account the inclusion and exclusion criteria given in Table 1. Participants will be allocated into four groups (the three intervention groups plus one control group) based on permuted block randomization. The allocation is concealed by using opaque, sealed envelopes that are consecutively numbered and included each group’s name. Sampling using this randomization process gives each participant an equal chance of being placed in each group [39].

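### Every test is set at 0.05 with no effect outcome ranked first, the 80% power covers one pairwise contrast and not the claim that the combination beats both single programmes, and the additive hypothesis has no matching contrast

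*Protocol article*

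**What the plan says.** Data analysis, Phase 2, of the protocol article sets one rule for all testing: "All tests will be performed at a significance level of 0.05 (p <0.05". It adds mean differences between groups with 95% confidence intervals. It names no adjustment, no order among comparisons and no interaction contrast.

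The claims to be supported are several. The Background expects the intervention groups to do better than control. It also expects the combination to have an additive effect and says that "this program will be more effective than each of the two separate intervention programs". The Secondary outcomes section asks "which intervention is the most effective for improving quality of life and work ability, and reducing WMSD symptoms and stress". All four effect domains are listed there as secondary; the two primary outcomes concern developing the model and designing the interventions. The section on the intervention programs says of the combined arm: "The multidisciplinary groups will receive both of the other two interventions in full". It also says that control participants will later be offered whichever programme proves most effective.

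On size, the Sample size and power calculations section says: "This sample size was calculated to be sufficient at an alpha of 0.05 and a power of .80, to test for a difference between the" arms. It continues that "we must consider a potential dropout rate of 30"% and that "we should work with an initial recruitment target of 40 participants in each group". Allocation is equal; the randomisation "gives each participant an equal chance of being placed in each group".

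**The concern.** Three statements do not fit together.

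- **Error rate.** A flat 0.05 for each test gives 5% error per test, not per trial. With four arms and no leading effect outcome, any favourable contrast on any outcome could be presented as the trial's result.
- **Power.** The calculation is for two groups and one difference. The main comparative hypothesis needs the combination to win twice, and the article gives no power for that.
- **Additivity.** Pairwise comparisons do not examine whether two effects add up. The design could: the arms cross biomechanical training (yes or no) with psychosocial training (yes or no), a complete 2x2 factorial. The stated analysis does not use this.

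At stake are how far a reported benefit can be trusted, and how a failure to show that the combination beats both singles should be read.

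**Working it through.** **Inputs** (Sample size and power calculations): SDs 20.2 and 21.1; difference 15; z values 1.96 and 0.84; 40 recruited per arm; dropout 30%. The article does not say which outcome or which pair of arms the 15 refers to.

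**1. The plan's own figure.** n = (1.96 + 0.84)² × (20.2² + 21.1²) / 15² = 7.84 × 853.25 / 225 = 29.73, so 30 per arm. The article prints 29.9, which also rounds to 30. The common SD is √(853.25/2) = 20.65.

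**2. Power of one contrast.** SE = 20.65 × √(2/n); power = Φ(15/SE − 1.96).

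| n per arm | SE | Power |
|---|---|---|
| 30 | 5.33 | 80.3% |
| 28 (= 40 × 0.7) | 5.52 | 77.6% |
| 40 (no dropout) | 4.62 | 90.1% |

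**3. Power to beat both single programmes.** The two test statistics share the combination arm, so with equal arms their correlation is 0.5. Power is the bivariate normal probability that both exceed 1.96.

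| n per arm | True gap 15 against each | True gap 10 against each |
|---|---|---|
| 28 | 65% | 28% |
| 30 | 69% | 30% |
| 40 | 83% | 42% |

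For 80% joint power at a gap of 15, about 38 evaluable per arm are needed. Allowing for 30% dropout, that is 38/0.7 = 54.3, so 55 recruited per arm.

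**4. Error of that joint claim.** With no true differences, the chance that both contrasts favour the combination significantly is about 0.5%. If the combination equals one single programme and is far better than the other, it is at most 2.5%. Requiring two rejections therefore costs power and does not raise error.

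**5. Error over separate tests.** Four equal arms were simulated with no true differences, one outcome, one visit, each test two-sided at 0.05:

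| Comparisons | Chance of at least one false rejection |
|---|---|
| Three arms against control | 12.4% |
| Those three plus combination against each single | 18.1% |
| All six pairs (4 × 3 / 2) | 20.2% |

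The article gives no correlation between outcomes. Assuming one score for each of the four domains and all six pairs, the chance runs from about 40% (correlation 0.8) to 60% (correlation 0).

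**6. Additivity.** The contrast is (combination − psychosocial) − (biomechanical − control), with SE = 20.65 × √(4/n). The 95% half-width is 1.96 × SE = 14.8 points at 30 per arm and 15.3 at 28. At 30 per arm, power to detect a departure from additivity is 51% if the departure is 15 points and 17% if it is 7.5.

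**The case against.** The strongest reply is that a journal article condenses a fuller plan. Contrast lists, adjustment methods and interaction terms often sit in a statistical analysis plan, and a 0.05 threshold is compatible with adjusted p-values. This stands in part: a missing contrast list would not be a finding by itself. But the article does not leave the level open. It states a rule for all tests, beside several between-arm claims and no leading effect outcome.

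On power, the article claims 80% only for a difference between groups, so it makes no false statement about the joint claim. The Discussion expects low attrition, and with 40 per arm joint power is 83%. Use of baseline data in the mixed model could also add precision. All this is fair. Still, the sample size section itself allows 30% dropout, and a 15-point advantage over an active single programme is an assumption that the article does not make explicit.

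On additivity, the Background may use the word loosely for better than either alone. This is the weakest part, and it is put only as a hypothesis without a matching contrast.

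Four stronger readings are tempting and not supported:

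- **That needing two rejections inflates error.** Step 4 shows the opposite.
- **That a false best programme is likely to be named.** A 20% chance of any false rejection on one outcome is not likely. Most such rejections would not single out a best arm, and picking the best arm is a ranking question that family-wise error does not measure.
- **That a definite number of false positives can be counted.** Eleven scores × 2 follow-ups × 6 pairs gives 132 tests and 132 × 0.05 = 6.6 expected false positives. But the article lists no such set of tests, the number of scores depends on whether HADS counts once or twice, and the figure assumes no effect anywhere.
- **That a factorial main-effects analysis is required.** Main effects do not answer which programme is best, and they can mislead if effects interact.

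**Conclusion.** The point holds in limited form and should be corrected.

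- **Error:** under the stated rule, the chance of at least one false between-arm rejection on one outcome at one visit is about 18% to 20% if no programme differs from any other. It is higher over several outcomes.
- **Power:** the 80% applies to one pairwise difference of 15. For the combination beating both singles it is about 65% to 69% at 28 to 30 evaluable per arm. This assumes a true gap of 15 against each, a common SD of 20.65, normal approximations and no gain from baseline adjustment. A smaller gap lowers it sharply.
- **Additivity:** the hypothesis has no matching contrast in the stated analysis. The design can estimate the interaction, but only to within about 15 points either way.

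**What to change.** 1. Name one effect outcome and one visit for the confirmatory claim.
2. Control the three comparisons with control at 5% overall, for example by Holm over three.
3. Test the combination against each single programme as a separate claim that requires both contrasts to succeed, each at unadjusted 0.05. Do not put these two into a five-way Holm family. At 30 per arm and a gap of 15, that would cut joint power from 69% to about 63% if effects add, or 50% if only the combination works.
4. Report other outcomes and visits as estimates with 95% intervals, without confirmatory claims.
5. Report the biomechanical-by-psychosocial interaction with its 95% interval, or drop the word additive.
6. State in the sample size section that 80% applies to a single pairwise contrast, and that power to beat both singles is about 65% to 69% on the same inputs.

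**Cost.** This is wording of the analysis and sample size sections; recruitment and procedures do not change. Each comparison with control loses some power. Holm's first step tests at 0.05/3, where z = 2.394, so at 30 per arm the floor is Φ(15/5.33 − 2.394) = 66% against 80% unadjusted. The two claims each carry their own error level, so together they are bounded by 5% + 2.5% = 7.5%, counting the combination claim in its favourable direction. The interaction estimate will be imprecise and should be presented as such.
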